| Safety End Points   | This study will be able to determine the safety of investigational therapeutics to determine if the rate of AEs is higher, lower, or no different than control arm.                                                                                                                                                                                                                                                                                                                                                                                                                                                                                                                                                                                                                                                                                                                                                                                                                                                                                                                                                                                                                                                                                                                             |

|                               |                                                                                                                                                                                                                                                                                                                                                                                                                                                                                                                                                                                                                                                                                                                                                      |

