### 2.2 Secondary Objectives

1. To evaluate the progress in clinical status of COVID-19 patients in both arms
2. To monitor the viral shedding duration and PCR test conversion days from positive to negative.
3. Evaluate the safety of investigational therapeutics as compared to the control arm.
4. To evaluate difference in the complications and prognosis of COVID-19 patients between the two groups.

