### 9.2 Sample Size and Power Considerations

#### 9.2.1 Assumptions and Study Hypothesis:

- a. **Time to discharge or clinical improvement by 2 points** in the standard of care arm is expected to be (median: 11 days; Cai Q, Y.M., Liu D, Chen J, Shu D, Xia J, , Experimental Treatment with Favipiravir for COVID-19: An Open-Label Control Study. 2020.).
- b. The exact treatment effect from Favipiravir tables + Hydroxchloroquine is not exactly known but can be approximated using prior clinical studies. A study comparing the effect of Favipiravir to lopinavir/ritonavir on virus clearance has shown a 64% reduction in time to viral clearance in the Favipiravir arm. This was equivalent to a median of 11 days. We assume that clinical improvement might take place a little later to viral clearance and therefore we assume that the treatment arm might result in a minimum clinically meaningful expected reduction of 30% (Median 7.7 days). This is equivalent to a Hazard ratio of 0.7.

- c. We further assume, that 50% of the patients in the control group will have clinical improvement/ discharged and 70% will have clinical improvement/discharged in the treatment arm
- d. It is anticipated that very few of these subjects will be randomized and not start study treatment (and so be excluded from the primary analysis) or be lost to follow-up (and so have missing data for the primary endpoint). Given certain uncertainties however, we have included a nominal 10% drop out rate.
- e. The primary hypothesis of the current study is  $H_0: HR = 1$  vs.  $H_1: HR \neq 1$  ; and HR is the hazard ratio of treatment compared to control arm.

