#### 9.2.2 **Sample Size Estimation for Classical Two Arm Parallel Design:**

Under the classical two arms parallel design the total effective sample sizes needed is 472 subjects (236 subjects per group). The Estimated sample size achieve 85 % power to detect a minimum of 30% reduction in the median time, to clinical improvement by at least two points or hospital discharge, in the treatment group compared to the control group. The median time in the treatment arm is 11 days under the null hypothesis and 7.7 days under the alternative hypothesis. The median time in control group under the null hypothesis is 11 days. The two survival curves will be analyzed using one sided cox proportional hazard regression. The significance level of the test is 0.025. Assuming 10% drop out rate, the overall sample size for the trial is estimated to be 520 (260 per group). Sample size adjustment will be considered after interim analysis of 60% of the subjects' recruitment and based on DSMB recommendation.

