### For secondary endpoints:

- Quantitative variables such as duration of ICU stay and change from baseline in clinical scores, etc., are expected to have reasonably skewed distributions and may be subject to censoring (e.g., for subjects in hospital on Day 28; these will be compared between randomized arms using non-parametric tests (e.g., Wilcoxon's Test adapted, if necessary, to handle censoring).
- Analysis of the ordinal scale endpoints will use a proportional odds model with an indicator variable for randomized treatment. The Wald test will be used to generate a p-value comparing treatments, as well as the estimated proportional odds ratio comparing treatments with associated 95% CI.

- Analysis of AE data will primarily be descriptive based on MedDRA coding of events. The proportion of subjects experiencing an SAE and the proportion experiencing a Grade 3 or higher AE will be compared between randomized arms using Fisher's Exact Test.

For enrolled subjects who were not randomized (i.e. screen failures) or who were randomized but did not receive the treatment, the final analysis will detail safety (deaths and SAEs), and reasons they were not randomized or did not received treatment respectively.

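### The Protocol Summary says the trial can establish that the AE rate is no different from control, but the sizing and the planned safety analysis cannot support that conclusion

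*Protocol*

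**What the plan says.** The Safety End Points row of the Protocol Summary says the study will have the ability "to determine if the rate of AEs is higher, lower, or no different than control arm".

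Section 9.4 (For secondary endpoints) sets out the analysis. "Analysis of AE data will primarily be descriptive based on MedDRA coding of events". For two summary proportions there is also a formal comparison: the proportion with an SAE, and "the proportion experiencing a Grade 3 or higher AE will be compared between randomized arms using Fisher's Exact Test". No margin or bound on the difference is attached to either.

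Section 9.2.1 sizes the trial on time to clinical improvement only. In its hypothesis "HR is the hazard ratio of treatment compared to control arm", and of the assumed reduction in median time it says "This is equivalent to a Hazard ratio of 0.7". It assumes that "50% of the patients in the control group will have clinical improvement/ discharged and 70% will have clinical improvement/discharged in the treatment arm". Section 9.2.2 gives 85% power with a one-sided Cox test, and "The significance level of the test is 0.025". The result is 472 effective subjects, raised to 520 (260 per group). No section gives an expected AE rate, a safety margin or power for a safety comparison.

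**The concern.** A test of difference can support the statement that a rate is higher or lower. Failure to reject does not support the statement that it is no different; that needs a margin, or at least an upper bound on the excess, judged acceptable in advance. The summary lists three possible conclusions, and the plan supplies tools for only two of them. The mismatch is wider for AEs as a whole, which are what the summary sentence names: Section 9.4 gives them no formal comparison.

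Safety is half of the stated aim of the study, and Section 1.5.5.1 lists bone marrow suppression, QTc prolongation and liver enzyme rises among the known risks. If the final report relied on the summary sentence, it could state equal safety when a modest excess of serious events had not been excluded.

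**Working it through.** **1. What the sample size was built for.** Inputs from Sections 9.2.1 and 9.2.2: HR 0.7, one-sided alpha 0.025, power 85%, 1:1 allocation, event proportions 50% and 70% (mean 60%).

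Events (Schoenfeld) = 4 × (1.960 + 1.036)² / (ln 0.7)² = 282.3, so 283.

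Subjects = 283 / 0.60 = 471.7, so 472. The stated figure is reproduced. Then 472 × 1.1 = 519.2, which the protocol gives as 520, or 260 per arm. The size is fully explained by efficacy, and no safety quantity enters it.

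**2. What Fisher's test can detect at that size.** Two inputs are assumptions, because the protocol does not give them: the control proportion (5% to 50% here) and a two-sided 5% level for Fisher's test. The power is exact: for every pair of counts (x control, y treated), add Bin(x; n, p_c) × Bin(y; n, p_t) over the pairs where Fisher's p ≤ 0.05 and y > x. The miss probability is one minus that sum.

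| Control v treated | Excess (points) | Missed, 260 per arm | Missed, 236 per arm |
|---|---|---|---|
| 5% v 10% | 5 | 47% | 52% |
| 10% v 15% | 5 | 64% | 68% |
| 20% v 25% | 5 | 76% | 78% |
| 30% v 35% | 5 | 80% | 82% |
| 10% v 20% | 10 | 13% | 16% |
| 20% v 30% | 10 | 28% | 33% |
| 30% v 40% | 10 | 37% | 41% |
| 50% v 60% | 10 | 41% | 46% |

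At 260 per arm the test reaches 50% power at an excess of about 5.0, 6.3, 7.8 and 8.8 points for control rates of 5%, 10%, 20% and 30%. It reaches 80% power at about 7.3, 9.0, 11.3 and 12.3 points.

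**3. What the trial could exclude.** If the observed rates are equal at p, the upper 95% limit for the risk difference is 1.96 × √(2p(1−p)/n). With n = 260:

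- p = 10%: 1.96 × √(0.18/260) = 0.052, or +5.2 points.
- p = 20%: 1.96 × √(0.32/260) = 0.069, or +6.9 points.

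Even identical observed rates would leave an excess of 5 to 7 points open.

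**4. If the trial stops early.** Section 9.3 allows a stop for efficacy or futility at 312 subjects, about 156 per arm. The same enumeration then gives miss rates of 69% (5% v 10%), 79% (10% v 15%), 85% (20% v 25%), 35% (10% v 20%) and 52% (20% v 30%).

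**The case against.** The strongest reply is that this is one loose sentence in a summary table. The safety objective in Section 2.2 is neutral ("Evaluate the safety of investigational therapeutics as compared to the control arm") and claims no equivalence. A trial sized on efficacy normally has no safety power statement. Section 9.4 calls itself a brief summary and defers detail to a SAP, where a confidence interval for the risk difference could properly sit. QT prolongation has its own secondary endpoint and ECG monitoring, and a DSMB reviews unblinded safety data.

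Much of this stands. The missing safety power is no error, the missing confidence interval would not be a finding on its own, and the overclaim is confined to the summary row. What does not follow is that the SAP or the DSMB repairs it. The sentence is protocol text about what the study can conclude. A SAP would still need a margin or bound to support it, and DSMB oversight during the trial does not turn a non-significant result into evidence of no difference.

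Three stronger readings are tempting and are not supported:

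- A reader might infer that a real harm would usually be reported as no difference. That depends on the control rate and the size of the harm, and the protocol gives neither. In the scenarios above, 10-point excesses are detected more often than missed at full size.
- A reader might infer that the sponsor intends to read a non-significant p-value as no difference. The protocol does not say so; it simply names no route to that conclusion.
- A reader might take the 1.8% frequencies in Section 1.5.5.1 as a base rate. They are single reactions associated with favipiravir, not control-arm proportions with an SAE or a Grade 3 or higher AE.

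**Conclusion.** The point holds as a mismatch between a stated capability and the design behind it. The summary promises a conclusion of no difference; the sizing is for efficacy only, AE analysis is mainly descriptive, and the one formal safety comparison has no margin or bound.

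The size depends on assumed control rates and an assumed two-sided 5% Fisher test. With 260 per arm and control rates of 5% to 20%, a 5-point excess is missed in 47% to 76% of trials. A 10-point excess is missed in 13% to 28% for control rates of 10% to 20%, and in up to 41% at a control rate of 50%. The logical part needs no assumption: at any control rate, non-significance alone does not show that the arms do not differ.

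No test, population or sample size is shown to be wrong. This should be corrected, and it is a matter of wording and reporting.

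**What to change.** In the Safety End Points row of the Protocol Summary, replace the claim to determine one of three outcomes with a statement that the study will estimate the between-arm difference in the proportion with an SAE and in the proportion with a Grade 3 or higher AE.

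In Section 9.4, report the risk difference with its two-sided 95% confidence interval beside each Fisher p-value. State that a non-significant result will be reported as no difference shown, with the upper confidence limit given as the largest excess not excluded. If the sponsor wishes to keep a conclusion of no difference, it should fix a margin before any comparative data are seen and require the upper limit to lie below it.

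The cost is a few lines of text and one interval per safety proportion, with no extra patients or procedures. The downside is a weaker safety statement: with equal observed rates and 260 per arm, the report would say that an excess of up to about 5.2 points (at 10%) or 6.9 points (at 20%) has not been excluded.

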## 1. INTRODUCTION

### 1.1. Background

Beginning in December 2019, a novel coronavirus, designated SARS-CoV-2, has caused an international outbreak of respiratory illness termed Covid-19. The WHO declared the epidemic of COVID-19 as a pandemic on March 12th, 2020^1. According to a recent Chinese study, about 80% of patients present with mild disease and the overall case-fatality rate is about 2.3% but reaches 8.0% in patients aged 70 to 79 years. In Saudi Arabia, as of March 27, 2020, 1012 confirmed cases of the disease were reported. Till now, there are no

specific therapeutic agents based on strong evidence, for this novel coronavirus infections, however, several medications have been evaluated as a potential therapy. Therapy warranted not only to treat symptomatic patients but also to decrease the duration of virus carriage in order to limit the transmission in the community.

Favipiravir which is a new type of RNA-dependent RNA polymerase (RdRp) inhibitor which has activity against influenza virus. In addition to its anti-influenza virus activity, favipiravir is capable of blocking the replication of flavi-, alpha-, filo-, bunya-, arena-, noro-, and other RNA viruses. Favipiravir is converted into an active phosphoribosylated form (favipiravir-RTP) in cells and is recognized as a substrate by viral RNA polymerase, thus inhibiting RNA polymerase activity, which theoretically can be active against SARS-CoV-2. Favipiravir compared to lopinavir/ritonavir in a study of 80 patients who has Covid-19, a shorter viral clearance time was found for the Favipiravir arm versus the lopinavir/ritonavir arm (median (interquartile range, IQR), 4 (2.5–9) d versus 11 (8–13) d,  $P < 0.001$ ). The Favipiravir arm also showed significant improvement in chest imaging compared with the lopinavir/ritonavir arm, with an improvement rate of 91.43% versus 62.22% ( $P = 0.004$ ). Furthermore, it was superior to Arbidol in having a higher 7-day clinical recovery rate in patients with Covid-19 and a more effective in reducing the incidence of fever and cough. While Chloroquine is a widely used antimalarial that was found to be a potential broad-spectrum antiviral in 2006. Chloroquine was found to block SARS-CoV-2 infection at low-micromolar concentration. Hydroxychloroquine, an analogue of chloroquine, has a clinical safety profile that is better than that of chloroquine and allows higher daily dose. In multicenter clinical trials conducted in China evaluating the efficacy of chloroquine or hydroxychloroquine, results from more than 100 patients have demonstrated that chloroquine phosphate is superior to the control treatment in inhibiting the exacerbation of pneumonia, promoting a virus-negative conversion, and shortening the disease course according to the news briefing. Thus, Hydroxychloroquine was included in many treatment pathways including Saudi Center of Disease and Prevention.

## 1.2. Study Medication:

### 1.2.1. Favipiravir

Favipiravir is a selective and potent inhibitor of influenza viral RNA polymerase. It acts as a purine analogue, which selectively inhibits viral RNA-dependent RNA polymerase (RdRps). Based on data from in vitro assay of influenza virus, favipiravir is incorporated into cells, undergoes phosphoribosylation and further phosphorylation to become favipiravir ribofuranosyl phosphates (RTP) which blocks viral RdRp. Hypothesis suggests that

favipiravir-RTP works by blocking polymerase domains, thus preventing incorporation of nucleotides for viral RNA replication and transcription.

Favipiravir has the characteristic of acting on RNA viruses including Ebola and Coronaviruses especially novel coronavirus (2019-nCoV). For Ebola virus, favipiravir was effective in preventing Ebola in mice by 100% although EC50 (drug concentration found to reduce viral replication by 50%) ~67 µM. Recent in vitro study on clinical isolates of 2019nCoV showed that Favipiravir has EC50 =61.88µM. 

### 1.2.2. Hydroxychloroquine

Hydroxychloroquine (HCQ) is an antimalarial agent with anti-inflammatory and immunomodulatory activities which has been gaining great interest recently for its antiviral activity. Data on using HCQ for Coronavirus is very limited. In vitro analyses on Vero cells demonstrated the potency of hydroxychloroquine in which EC50= 0.72 µM against SARS-CoV-2. 

HCQ antiviral activity is believed to be related to its ability to inhibit SARS-CoV entry through changing the glycosylation of ACE2 (Angiotensin Converting Enzyme-2) receptor and spike protein and also inhibits post-entry stages of SARS-CoV-2 by blocking the transport of SARS-CoV-2 from early endosomes to endolysosomes, which appears to be a requirement to release the viral genome. 

### 1.3. Dose Adjustment 

Table 1 Dose Adjustment for study medication

|                         | Favipiravir                                                                      | Hydroxychloroquine                                                               |
|-------------------------|-----------------------------------------------------------------------------------------|-----------------------------------------------------------------------------------------|
| Renal impairment | No recommendations for dosage adjustment provided by the manufacturer in package insert | No recommendations for dosage adjustment provided by the manufacturer in package insert |

|                           |                                                                                                                                                                                                                   |                                                                                                                            |
|---------------------------|-------------------------------------------------------------------------------------------------------------------------------------------------------------------------------------------------------------------|----------------------------------------------------------------------------------------------------------------------------|
| Hepatic impairment | Higher plasma levels reported with severe hepatic impairment (Child Pugh Class C).
Dosage regimen used for patients with Child Pugh Class C: 800 mg BID for one day, followed by 400 mg BID per package insert | No recommendations for dosage adjustment provided by manufacturer in package insert. Instead, cautionary use was suggested |
|---------------------------|-------------------------------------------------------------------------------------------------------------------------------------------------------------------------------------------------------------------|----------------------------------------------------------------------------------------------------------------------------|

#### 1.4. Drug interaction

##### Favipiravir Drug Interactions 

- Favipiravir inhibits aldehyde oxidase irreversibly, inhibits CYP2C8 and to a lesser extent CYP1A2, 2C9, 2C19, 2D6, 2E1 and 3A4.
- Drugs that interact with favipiravir:
  - Theophylline increases favipiravir Cmax and AUC by about 30%.
  - Pyrazinamide increases uric acid serum level when administered concomitantly with favipiravir due to increase reabsorption of uric acid in the renal tubules
  - Repaglinide plasma level may increase due to CYP2C8 inhibition
  - Famciclovir plasma level may be decreased due to aldehyde oxidase inhibition
  - Use Favipiravir must be with caution while using acetaminophen – dosing of acetaminophen should be no more than 3000mg/day (or less in patients with hepatic insufficiency)

##### HYDROXYCHLOROQUINE DRUG INTERACTIONS 

- HCQ is metabolized by CYP enzymes (CYP2D6, 2C8, 3A4, and 3A5) into 3 metabolites: desethylhydroxychloroquine, desethylchloroquine, and bidesethylchloroquine.
- Data from previous study done by the Plaquenil Lupus Systemic Study Group in which authors analyzed blood HCQ concentrations in patients receiving enzyme inducers or inhibitors. They concluded that no pharmacokinetic interaction has been observed between these drugs and blood HCQ concentration based on similar mean plasma drug concentration of HCQ achieved.

- No data are available to evaluate effect of favipiravir (CYP 2C8 inhibitor) on HCQ plasma concentration.
- We concluded that no clear risk of HCQ accumulation when used concomitantly with favipiravir based on data extrapolated from previously mentioned study
- However, we recommend to exercise caution when starting HCQ with following medications.
- Digoxin serum levels may increase with concomitant use of HCQ. Serum digoxin levels should be closely monitored
- Insulin hypoglycemia effect may be enhanced with HCQ. Dosage adjustment of insulin/antidiabetic drugs may be required. Patients treated with hydroxychloroquine should be monitored for hypoglycemia. We recommend frequent blood glucose monitoring. In cases of severe hypoglycemia, hydroxychloroquine should be discontinued.
- Drugs that prolong QT interval and other arrhythmogenic drugs can potentiate QTc prolongation associated with HCQ. HCQ should not be administered with other drugs that have the potential to prolong QTc.
- Antiepileptics drugs effect might be compromised with HCQ due to lower seizure threshold
- Cyclosporin serum level may increase when administered with HCQ. Cyclosporin serum level monitoring is recommended.

